### Design

SPAR is a randomised, double-blind, placebo-controlled, multicentre phase II trial. Eligible patients will be allocated to one of two treatment groups (SIM or placebo) in a 1:1 ratio (Fig. 1: SPIRIT diagram).

**Fig. 1 Fig1:**
[figure not shown]
SPAR SPIRIT diagram. Abbreviations: HGD; high grade dysplasia. LC; long course. pCRT; preoperative chemoradiation. FP; fluoropyrimidine. cT/cN; clinical stage. LVI; lymphovascular invasion. ®; randomisation. Gy; gray. fx; fraction. BD; twice daily. 5FU; 5-fluorouracil. mrTRG: magnetic resonance assessed tumour regression grade

Treatment allocation will be balanced using minimisation for the following characteristics:
trial siteAJCC clinical T stage (< 4 vs. 4)AJCC clinical N stage (< 2 vs. 2)the presence of either mesorectal fascia involvement (tumour margin within 1 mm of the fascia) or lymphovascular space invasion (including extramural venous invasion) on MRI

### Eligibility criteria

The target population is adult patients with biopsy-proven rectal adenocarcinoma (or high-grade dysplasia on biopsy with radiological evidence of invasive tumour) planned for concurrent long-course pCRT using a standard fluoropyrimidine-based chemotherapy schedule.

#### Inclusion criteria

Males or females with biopsy proven rectal adenocarcinoma, or high-grade dysplasia with radiological evidence of invasive tumour.Distal border of the tumour is below the peritoneal reflection as assessed by MRI scan.Age ≥ 18 years.Clinical TNM tumour staging is T2–4 N0–2 M0 after staging investigations including CT scan of chest, abdomen and pelvis and pelvic MRI scan. Patients with resectable M1 (e.g. oligometastatic liver or lung) disease who are being treated with curative intent can be eligible, following approval from the SPAR Study Chair.Planned for concurrent long-course pCRT using fluoropyrimidine-based chemotherapyRadiologically measurable disease on baseline pelvic MRI scan.Adequate bone marrow, liver and renal function (platelets > 100 × 10^9^/L, neutrophils > 1.5 × 10^9^/L, ALT/AST < 3 x ULN, bilirubin < 1.5 x ULN, estimated creatinine clearance > 50 ml/min).Trial treatment planned to start within 28 days of randomisation.Diagnostic biopsy of rectal tumour is available for histological substudies.Willing and able to comply with all trial requirements.Signed, written informed consent for the main trial.

#### Exclusion criteria

Contraindications or hypersensitivity to statins, fluoropyrimidine chemotherapy or radiotherapyPatients planned to receive oxaliplatin or biological agents (e.g. cetuximab) as part of pCRTTaking statins in the 6 weeks before planned start of pCRTPredicted life expectancy of less than 3 yearsPrior pelvic or rectal radiotherapyHistory of another malignancy within 5 years prior to registration (not including adequately treated carcinoma-in-situ, basal cell carcinoma of the skin, squamous cell carcinoma of the skin, or superficial transitional cell carcinoma of the bladder). Patients with a history of other malignancies are eligible if they have been continuously disease free for at least 5 years after definitive primary treatmentConcurrent illness, including severe infection that may jeopardise the ability of the patient to undergo the procedures outlined in this protocol with reasonable safetySerious medical or psychiatric conditions that might limit the ability of the patient to comply with the protocolPregnancy, lactation, or inadequate contraception.

### Treatment

Simvastatin or placebo is the trial intervention. Concurrent preoperative chemoradiation (pCRT) using fluoropyrimidine-based chemotherapy and radiotherapy is required standard concomitant treatment (Fig. 1).

One simvastatin 40 mg capsule or one matching placebo capsule taken orally each evening, will commence 7 (+/− 3) days prior to pCRT and continued for 90 consecutive days. Subject compliance with the trial treatment will be determined at protocol-specified assessments by questioning the participant and a formal count of the capsules returned at completion of study treatment (6 weeks after pCRT).

Trial treatment (SIM or placebo) will be permanently discontinued if progressive disease (PD) is documented, unacceptable treatment-related toxicity occurs, a delay of pCRT of > 28 days occurs, the clinician believes that continuation of trial treatment is not in the patient’s best interest, or the patients fails to comply or declines further treatment.

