## Methods/design

SPAR is a randomised phase 2 study with the overall aim to evaluate the effect of SIM on efficacy and toxicity of pCRT in rectal cancer patients, and on systemic and local inflammatory responses. Recruitment of 222 patients is required to address the primary objective. The study will recruit patients from participating AGITG hospitals/institutions in Australia and New Zealand.

Primary Objective:

The primary objective is to compare rates of favourable (grades 1–2) mrTRG (by central review) following pCRT with SIM versus with placebo, considering mrTRG in 4 ordered categories: 1, 2, 3, 4–5 (proportion of patients with favourable mrTRG in SIM and placebo groups). mrTRG will be assessed by comparison of the MR scan taken after pCRT with the scan before pCRT, which will be performed using the MERCURY protocol (38), and images analysed as described [38].

Secondary Objectives:

Secondary objectives are to compare between the SIM and placebo groups treated with pCRT: 1) The rate of favourable (grades 1–2) pathTRG in resected tumours by central review (proportion of patients with favourable pathTRG at surgical resection); 2) The incidence of > grade 2 acute GI and non-GI adverse events, assessed using CTCAE version 4.03; 3) The incidence of late GI adverse events; 4) Compliance with intended pCRT (proportion of patients completing > 90% of planned pCRT without dose reductions or delays); 5) Compliance with trial medication (proportion of patients receiving > 90% of the planned trial medication); 6) The proportion of patients undergoing surgical resection post-pCRT; 7) 3-year local recurrence (LR) rate, disease-free survival (DFS) and cancer-specific survival (CSS) (3-year LR rate, DFS and CSS); 8) the pathological scores determined by the central pathologist for radiation colitis in irradiated rectum in the resected specimen (radiation colitis scores).

Translational Science Objectives:

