### Radiation therapy

It is recommended to follow eviQ Rectal (Neoadjuvant EBRT Chemoradiation Pre-operative Long Course) Guidelines version 2 or later (www.eviq.org.au).

Clinical Target Volume A (CTV A) is defined as per the recent international consensus guidelines [61]. The Planning Target Volume (PTV) A margin should be 0.7 to 1.0 cm, except at skin, where planning system requirements mandate it be trimmed to 2–5 mm within the skin surface. The dose to PTV A is 45Gy in 25 fractions, 1.8Gy per day, 5 days per week.

Clinical Target Volume B (CTV B) includes the mesorectum and pre-sacral region at involved levels with a 1–2 cm margin cephalad and 1 to 2 cm on gross tumour within the rectum. The PTV B margin should be 0.7 to 1.0 cm, except at skin, where planning system requirements mandate it be trimmed to 2–5 mm within the skin surface.

For 3-dimensional conformal radiation therapy (3DCRT), a tumour boost of 5.4Gy at 1.8Gy per fraction to PTV B (50.4Gy cumulative including contribution from PTV A) is required for patients with T3 tumours. A boost dose up to 10.8Gy at 1.8Gy per fraction (55.8Gy cumulative, including contribution from PTV A) is allowed for patients with T4 fixed cancer and high-risk T3 tumours.

For intensity modulated radiation therapy (IMRT) or volumetric modulated arc therapy (VMAT), simultaneous boost technique is recommended. Total cumulative dose to PTV B is to be 50 Gy.

Permission for other radiation techniques aiming to deliver equivalent radiation dose should be obtained in advance from Trial Management Committee.

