### Post-operative management

Treatment after discontinuation of trial treatment is at the discretion of the patient’s clinician. Adjuvant chemotherapy may be administered on the recommendation of the treating clinician and its use will be recorded.

Blood tests will be performed on the first day of pCRT, prior to starting chemotherapy, to assess the impact of trial medication on the mGPS and NLR. Clinical assessments including IBDQ-B questionnaire will be conducted on Trial Weeks 3, 5 and 7 [62].

Week 13 assessments will be performed 6 weeks (+/− 7 days) after completion of pCRT and prior to surgery. An MRI scan for mrTRG must be completed 6–8 weeks after completion of pCRT and must be prior to surgery. The postoperative visit will include assessment of length of hospital stay after surgery and any readmission data. Subsequent follow-up is annually.

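### The capsule count 6 weeks after chemoradiation can fall before day 90, so a fully adherent patient can miss the >90% compliance threshold

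*Protocol article*

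**What the plan says.** All references are to the protocol article.

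- **Treatment:** one capsule is taken each evening. The course "will commence 7 (+/− 3) days prior to pCRT" and is "continued for 90 consecutive days". Compliance "will be determined at protocol-specified assessments by questioning the participant" and by "a formal count of the capsules returned at completion of study treatment (6 weeks after pCRT". The count is thus tied to the end of trial treatment, and that end is placed 6 weeks after chemoradiation (pCRT).
- **Methods/design, secondary objective 5:** the endpoint is the "proportion of patients receiving > 90% of the planned trial medication".
- **Radiation therapy:** "The dose to PTV A is 45Gy in 25 fractions, 1.8Gy per day, 5 days per week". With 3DCRT, a boost of 5.4 Gy, or up to 10.8 Gy, is added at 1.8 Gy per fraction. With IMRT or VMAT a simultaneous boost is recommended, and the number of fractions is not stated.
- **Post-operative management:** "Week 13 assessments will be performed 6 weeks (+/− 7 days) after completion of pCRT and prior to surgery".
- **Table 1:** pCRT occupies weeks 2 to 7. Compliance with trial medication is marked at weeks 3, 5, 7 and 13, and at no later visit.

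**The concern.** The Treatment section gives two ends for the same course: day 90 from the first capsule, and 6 weeks after pCRT. The first depends only on the start date. The second also depends on how long radiotherapy lasts. They agree when pCRT fills six calendar weeks, but a 25-fraction course takes about five.

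If the count comes first, some capsules in the returned bottle are not yet due. With 90 as the denominator they look the same as missed doses. The threshold is strict and sits close to the nominal count, so a few capsules decide whether a patient is classed as compliant. Part of the variation in objective 5 would then come from fraction number, weekday of start and visit date among patients who missed nothing.

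**Working it through.** **Inputs**
- Planned capsules: 90 (Treatment).
- Lead-in *L*: 7 days, permitted 4 to 10 (Treatment).
- Last fraction to count *V*: 42 days. Table 1 puts the last compliance check at week 13, whose window is ±7 days (Post-operative management), so 35 to 49.
- Fractions: 25; 25 + 5.4/1.8 = 28; or 25 + 10.8/1.8 = 31 (Radiation therapy). The simultaneous-boost course is assumed to have 25.
- Calendar span *S* at 5 fractions per week without interruption, first and last day included: 25 fractions take 33 days from a Monday start and 35 from a Tuesday to Friday start; 28 take 38 to 40; 31 take 43.

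**The plan's own figure.** From Table 1: 7 days (week 1) + 42 days (weeks 2–7) + 42 days = 91 days, which is 90 evenings before a visit on day 91. The 90-day course is reproduced, but only with six full weeks of pCRT.

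**Threshold.** 0.90 × 90 = 81. Since the rule is strictly greater than 90%, 81 fails and 82 is needed.

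**Formula.** With perfect adherence, capsules taken by the count = *L* + *S* + *V*, minus 1 if the count precedes that evening's dose, to a maximum of 90. Ranges below cover every weekday start, with and without that dose.

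| Fractions | Lead-in | Visit (days) | Capsules of 90 | Above 90%? |
|---|---|---|---|---|
| 25 | 7 | 42 | 81–84 (90.0–93.3%) | Yes, except 81 |
| 25 | 4 | 42 | 78–81 (86.7–90.0%) | No |
| 25 | 7 | 35 | 74–77 (82.2–85.6%) | No |
| 25 | 10 | 42 | 84–87 (93.3–96.7%) | Yes |
| 25 | 7 | 49 | 88–90 (97.8–100%) | Yes |
| 28 | 7 | 42 | 86–89 (95.6–98.9%) | Yes |
| 28 | 7 | 35 | 79–82 (87.8–91.1%) | Only at 82 |
| 31 | 7 | 42 | 90 (100%) | Yes |

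In the first row, the lower end is 7 + 33 + 42 − 1 = 81 (Monday start, counted before the evening dose) and the upper end is 7 + 35 + 42 = 84. The shortfall from 90 is therefore 6 to 9 capsules. The Monday start counted before the dose is the only nominal case that fails, by one capsule.

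**All permitted combinations.** There are 7 lead-in days × 15 visit days × 5 weekday starts = 525 combinations per course. With equal weights, the share at 81 capsules or fewer is:
- 25 fractions: 36.0% if the visit-evening dose is credited, 42.7% if not;
- 28 fractions: 10.9% and 15.8%;
- 31 fractions: 0% and 1.0%.

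The equal weights are an assumption and do not forecast actual visit dates.

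**The case against.** **The nominal timeline is coherent.** Table 1 adds up to about 90 days, the 3DCRT boost for T3 tumours gives 28 fractions, and 28 fractions pass at nominal timing. This stands. A reader might infer that every adherent patient on 25 fractions fails; the document does not support that. Most pass at nominal timing, and a longer lead-in or a later visit helps them. The share of patients on 25 fractions is unknown, and any interruption of radiotherapy would narrow the gap.

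**Failure depends on a scoring rule that the article does not spell out.** Participants are also questioned, and nothing says that capsules not yet due are scored as missed. Such conventions are often left to the full protocol or analysis plan. This stands in part: the figures are conditional on 90 as the denominator and on the count being final. The conflict itself is not an omission, however. The Treatment section states both end points, Table 1 shows no later compliance check, and questioning at the visit cannot confirm doses that are not yet due.

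**The effect is the same in both arms.** Allocation is double-blind and minimised by site, so a between-arm bias should not be inferred. The primary endpoint does not use the count, and the per-protocol set depends on taking trial medication when pCRT starts. It would also go too far to say that objective 5 measures scheduling and not adherence; scheduling only contaminates it.

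**Conclusion.** The point holds in a conditional form. Day 90 and 6 weeks after pCRT do not coincide on a 25-fraction course. With 90 as the denominator and the strict threshold, a perfectly adherent patient usually passes at nominal timing but can fail inside the protocol's own windows. The margin is thin even for those who pass: 82 to 84 capsules at the count leave room for 0 to 2 missed doses, where a full 90-day count would leave 90 − 82 = 8.

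The consequence is an understated absolute compliance rate in one secondary objective, probably equally in both arms. Its size in the trial cannot be given, because the mix of fraction numbers and the actual visit dates are unknown. The result rests on four assumptions: uninterrupted radiotherapy, 25 fractions for the simultaneous boost, the week 13 window applying to the count, and no credit for capsules due after it. The point is worth correcting because the correction is cheap, but it does not threaten the trial's main conclusion.

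**What to change.** Define compliance in objective 5 as capsules taken divided by capsules due from the first dose to the date of the count, to a maximum of 90, and state whether the dose on the evening of the visit is counted as due. A fully adherent patient then scores 100% whatever the fraction number or visit date; for example, 74 of 74 in place of 74 of 90.

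Reconcile Methods/design (objective 5), Treatment and Post-operative management on what ends the course of trial medication and when capsules are counted. Which treatment duration is intended is for the trial team to say, and the new definition does not require a change in dosing.

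The cost is one definition sentence and consistent wording across those sections, with no new visit. The downside is that adherence after the count is not captured for patients counted before day 90, and the report should say so.

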### Radiation therapy

It is recommended to follow eviQ Rectal (Neoadjuvant EBRT Chemoradiation Pre-operative Long Course) Guidelines version 2 or later (www.eviq.org.au).

Clinical Target Volume A (CTV A) is defined as per the recent international consensus guidelines [61]. The Planning Target Volume (PTV) A margin should be 0.7 to 1.0 cm, except at skin, where planning system requirements mandate it be trimmed to 2–5 mm within the skin surface. The dose to PTV A is 45Gy in 25 fractions, 1.8Gy per day, 5 days per week.

Clinical Target Volume B (CTV B) includes the mesorectum and pre-sacral region at involved levels with a 1–2 cm margin cephalad and 1 to 2 cm on gross tumour within the rectum. The PTV B margin should be 0.7 to 1.0 cm, except at skin, where planning system requirements mandate it be trimmed to 2–5 mm within the skin surface.

For 3-dimensional conformal radiation therapy (3DCRT), a tumour boost of 5.4Gy at 1.8Gy per fraction to PTV B (50.4Gy cumulative including contribution from PTV A) is required for patients with T3 tumours. A boost dose up to 10.8Gy at 1.8Gy per fraction (55.8Gy cumulative, including contribution from PTV A) is allowed for patients with T4 fixed cancer and high-risk T3 tumours.

For intensity modulated radiation therapy (IMRT) or volumetric modulated arc therapy (VMAT), simultaneous boost technique is recommended. Total cumulative dose to PTV B is to be 50 Gy.

Permission for other radiation techniques aiming to deliver equivalent radiation dose should be obtained in advance from Trial Management Committee.

### Chemotherapy

The accepted chemotherapy and dosing regimens [6] are one of:
capecitabine 825 mg/m^2^/day PO BID 5 days a week on days of RT administrationcapecitabine 825 mg/m^2^/day PO BID 7 days a week for the duration of RT5-fluorouracil 225 mg/m^2^/day via continuous venous infusion for the duration of RTOther therapies and/or dosing regimen that have been accepted as standard of care in Australia and New Zealand may be allowed following agreement from the Study Chair

A maximum BSA of 2.2 m^2^ is recommended for dosing of fluoropyrimidine-based chemotherapy. Clinicians must pre-specify which schedule they will be using for each participant. Once allocated, the patients must then adhere to the specified schedule throughout the treatment period, unless modified for safety reasons.

### Dose modifications and supportive therapies

Patients should be managed with pCRT according to institutional protocols, including dose modifications and delays for treatment-related toxicities. Recommendations are provided for guidance on management of toxicities related to pCRT and are defined in the protocol. If pCRT is discontinued, trial treatment should continue unless unacceptable trial treatment toxicity is observed. Other concomitant medications and supportive therapies are permitted, and there is a list of prohibited medications (drugs that may interact with the trial drug) in the detailed protocol.

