### Statistical methodology

#### Sample size

The primary endpoint of this trial is rates of favourable mrTRG (grades 1 or 2). This will be analysed using ordinal regression with 4 ordered categories of mrTRG (1, 2, 3 and 4–5) to provide greater sensitivity. Based on published data using MRI 6–8 weeks after pCRT, the expected rate of mrTRG in the control group is 9% grade 1, 39% grade 2, 20% grade 3 and 32% grades 4–5. A 35% relative increase in favourable mrTRG would be a worthwhile difference to inform a phase III trial.

Based on an ordinal proportional odds assumption, a sample size of 222 patients (111 treated with SIM and 111 controls) will have > 80% power to detect a change in mrTRG rates to 17% grade 1, 48% grade 2, 16% grade 3 and 19% grades 4–5 with 95% confidence.

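### The article gives opposite trial-drug instructions for a patient whose pCRT is interrupted and never resumed, and its capecitabine unit has two readings that differ two-fold

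*Protocol article*

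**What the plan says.** **Trial drug.** The Treatment section of the protocol article lists the reasons for ending trial drug and makes them mandatory: "Trial treatment (SIM or placebo) will be permanently discontinued if progressive disease (PD) is documented". The list goes on to other triggers, one of which is that "a delay of pCRT of > 28 days occurs". The later section on dose modifications and supportive therapies says: "If pCRT is discontinued, trial treatment should continue unless unacceptable trial treatment toxicity is observed". The planned course is a daily capsule that "will commence 7 (+/− 3) days prior to pCRT and continued for 90 consecutive days". Secondary objective 5, under Methods/design, measures compliance as the "proportion of patients receiving > 90% of the planned trial medication".

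**Capecitabine.** The Chemotherapy section gives the first accepted option as "capecitabine 825 mg/m^2^/day PO BID 5 days a week". The second option, given seven days a week, carries the same unit. The section adds: "A maximum BSA of 2.2 m^2^ is recommended for dosing of fluoropyrimidine-based chemotherapy".

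**The concern.** The two trial-drug rules turn on neighbouring events. A pause in pCRT that lasts beyond 28 days leads to a permanent stop, and an end to pCRT leads to continuation. A pause that turns out to be final fits both descriptions, and the article offers nothing to choose between them. Two sites could then handle identical patients in opposite ways, giving them different trial-drug exposure and different results on a stated secondary endpoint. Because the primary analysis is by intention to treat, these patients stay in it whichever rule was applied.

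The capecitabine lines raise a separate issue. A per-day unit makes 825 mg/m² the day's total, while BID allows it to be the amount of each of two doses. This is a stated cytotoxic dose, so an unclear unit is first a safety matter. It also bears on the acute toxicity comparison and on what counts as the planned chemotherapy.

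**Working it through.** Neither point rests on a figure that the article derives, so there is no plan calculation to reproduce. The sample size does not depend on either instruction.

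**1. The stop rule**

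Inputs from the article:
- Lead-in L = 7 days, range 4 to 10 (Treatment).
- Planned trial drug: 90 daily doses (Treatment).
- Delay trigger: more than 28 days (Treatment).
- Length of pCRT: 5 to 6 weeks, so at most 42 days (Background).
- Compliance threshold: more than 0.90 × 90 = 81 doses (Methods/design).

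Assumptions: every capsule is taken until trial drug stops, there is no earlier pCRT interruption, and pCRT halts for good after k days.

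Under the delay rule, doses taken when the 28 days are complete = L + k + 28. Under the discontinuation rule, doses taken = 90.

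| L | k (days of pCRT before halt) | Delay rule: doses | Delay rule: share of 90 | Discontinuation rule |
|---|---|---|---|---|
| 7 | 7 | 42 | 47% | 100% |
| 7 | 14 | 49 | 54% | 100% |
| 7 | 21 | 56 | 62% | 100% |
| 7 | 28 | 63 | 70% | 100% |
| 7 | 35 | 70 | 78% | 100% |
| 10 | 42 | 80 | 89% | 100% |

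The last row is the extreme case: the longest lead-in and the full six weeks. Allowing one further day for the delay to exceed 28 days gives 81 doses, which is still not more than 81. So, under these assumptions, a halt at any point in the course brings the two rules into conflict before day 90. The delay rule then always produces a compliance failure, and the discontinuation rule allows a pass.

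**2. The capecitabine unit**

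- Read as a daily total: 825 mg/m² per day.
- Read as the amount of each of two doses: 2 × 825 = 1650 mg/m² per day.
- Ratio: 1650 / 825 = 2.
- At the recommended BSA ceiling of 2.2 m²: 825 × 2.2 = 1815 mg per day, or 1650 × 2.2 = 3630 mg per day.
- Over 25 radiotherapy days on the five-day schedule (25 fractions, Radiation therapy section): 825 × 25 = 20,625 mg/m², or 1650 × 25 = 41,250 mg/m².

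No other line in the article gives a per-dose amount or a daily total that would settle the reading. The neighbouring 5-fluorouracil entry also uses a per-day unit, but for a continuous infusion, where the question of divided doses does not arise.

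**The case against.** **Delay and discontinuation are different events.** A delay implies that pCRT is still intended, and a discontinuation means that it has ended. This is fair, and a reader who inferred that the rules conflict for every patient with disrupted pCRT would go too far. What remains is the patient whose pause becomes permanent. Nothing in the article says when that patient passes from one category to the other.

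**The full protocol may resolve both points.** It may, and sites work from it. The article refers to it for toxicity guidance and prohibited drugs, cites a source for the chemotherapy regimens, and leaves pCRT management to institutional protocols. But these are instructions that the article states, not details that it leaves out, so they should be readable in one way.

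**Other stop reasons.** A reader might infer that the discontinuation sentence also overrides progression, clinician judgement or patient refusal, because it names only toxicity as an exception. The text does not support this. The sentence follows guidance on pCRT toxicity and can be read as saying only that ending pCRT is not in itself a reason to end trial drug. The general stopping list can still apply alongside it.

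**Capecitabine is background treatment in both arms.** Trial site is a minimisation factor, so differences between sites would tend to balance across arms. This stands against any claim of bias in the treatment comparison. It does not remove the safety reason for a clear unit.

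**Conclusion.** Both points hold in limited form.

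For trial drug, the article gives opposite instructions for a patient whose pCRT is interrupted and never resumed. Planned doses received are about 47% to 78% under one rule (7-day lead-in, halt after 7 to 35 days of pCRT) against up to 100% under the other, and the compliance result can change with them. The halt dates are assumptions, and the article does not say how many such patients to expect.

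For capecitabine, a reader might infer that the article states two different doses. It does not. It states one figure with an internally inconsistent unit, and the two readings differ by a factor of two in both schedules.

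A reader might also infer that the compliance endpoint is defective because it does not say how a rule-driven stop counts. That derivation belongs to the analysis plan and is not a fault here. Sample size, power and the type I error rate are unaffected.

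**What to change.** The investigators should reconcile the Treatment section with the section on dose modifications in a single rule that covers both delay and discontinuation of pCRT, so that a pause that becomes permanent has one stated consequence for trial drug. They should also reconcile the units of both capecitabine options with the cited source regimen and the full protocol, so that each line has one reading. The choice of rule and dose is theirs.

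The cost is clarifying text or a letter to sites. No design change or recalculation is needed. The article describes the trial as still accruing, so the clarification would be of use to patients yet to be treated.
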